### Sample size calculation

Assuming a calculated proportion of 0.76 for successes in the subgroup of patients additionally fulfilling the inclusion cirteria of the RCT, and a sample size of 300 for this subgroup, the width of the 95% CI, calculated using Wilson's method, will be 0.096 with the lower bound 0.709 and the upper bound 0.805
[22]. Given an estimated enrolement of 4 patients per center/year at 45 study centers plus one year of follow-up, data acquisition would be concluded in 3 years. Thus the end of the study is planned for 2014.

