[13]. Indeed, some authors and the latest meta-analysis defined favorable as a mRS of ≤ 3
[4]. Other authors think that the question of favorable (or in such severe diseases rather “acceptable”) outcome should be answered by the patients themselves. Unfortunately, the contradictory data on quality of life and retrospective consent to hemicraniectomy after malignant MCA infarction that are currently found in the literature are of little help in preoperative decision making
[5,9,14-18]. Fourth, the actual effectiveness of conservative treatment has never been addressed in detail, e.g. the RCT showed different outcomes in the conservative treatment groups: patients who were treated on an intensive care unit
[5] had a higher rate of survival (47% vs. 22%) and more often better functional outcome (mRS 0–4: 33% vs. 0%) than patients treated on a stroke unit or a general ward
[6]. Fifth, despite the life-saving character of DHC, the overall case fatality rate in patients who underwent surgery in the RCT was still 29%
[7]. This means that nearly every third patient dies for reasons not well understood. Similarly, no valid data are available on the actual rate of complications especially concerning re-implantation of the skull.

Most of these issues are a commonplace in the scientific community and have been addressed in a number of case series and non-randomized case control studies
[19-21]. However, most of these studies are retrospective in nature, lack appropriate control groups, and show heterogeneous or inconclusive results. Therefore, proper investigation in a large-size, prospective study is urgently needed. Besides, the implementation of hemicraniectomy in clinical practice has not been reviewed since the publication of the RCT.

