## Methods

### Study design

DESTINY-R is a prospective, multicenter, open, and controlled registry. There will be no active allocation of the patients either to hemicraniectomy or any conservative treatment option. At the time of publication 45 neurologic and neurosurgical departments were registered as actively recruiting study centers. All participating centers have adequate experience with the management of acute ischemic stroke, intensive care treatment of patients with increased intracranial pressure (ICP) and access to neurosurgical facilities on a 24-hours/day basis.

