### Data analysis

All outcome measures will undergo descriptive data analysis, including mean, standard deviation, median, range, as well as absolute and relative frequencies depending on the scales of the variables. Additionally, descriptive *p*-values for group comparison and the corresponding 95% confidence interval will be indicated. Two-sample *t* testing, the Mann–Whitney *U*-test, or *χ*2-testing will be used to analyze group differences as applicable. Kaplan-Meier estimates and log-rank statistics will be used for assessing cumulative risk of death at 12 months. The comparability of different treatment groups will be depicted by comparing demographic and baseline data. Statistical analysis will be performed using the latest SAS software version (SAS Institute Inc., Cary, NC).

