## Discussion

We advocate the use of a prospective register to further characterize patients with malignant MCA infarction and evaluate implementation, effectiveness and adverse events of current treatment concepts, including DHC. Although first trends in prevalence and outcome of DHC are promising and seem comparable to the results of the RCT
[23,24], the use of a large database allows the representation of a much broader population of patients treated for malignant MCA infarction. The anticipated sample size should allow confirming the results of the RCT and raising new hypotheses even if the population turns out to be more heterogeneous than expected. The planned inclusion of at least 300 patients in a reasonable time frame can only be achieved in a multicenter approach. The open design allows continuing initiation of cooperative study centers. The very conservative estimate of 4 patients/year per center would probably allow extending patient recruitment to 500 or even 1000 if certain questions would need a larger sample size to be investigated. However, due to the nature of a prospective registry, only hypotheses may be created, which then need further investigation in RCT.

To avoid the investigation of a very restricted group of patients, the inclusion criterion of infarct size was intentionally set comparatively wide. Thus any patient with a MCA infarction involving more than 50% of the territory can be included irrespective of treatment, although eligibility criteria for the RCT were infarction of more than 2/3 of the MCA territory. However, as the individual factors promoting infarct swelling are not well understood yet, not considering these patients may possibly exclude a subgroup of patients that would have the potential to benefit from a certain treatment option in the future. The limited number of eligibility criteria are easy to implement even in small hospitals with limited staff and will most likely result in a patient mix representative of clinical practice. Conservatively treated patients are followed simultaneously and constitute the control group, which may be compared to surgically treated patients in this parallel design. Due to treatment bias it may be possible that treatment groups show significantly different baseline data making a true comparison difficult. The expected number of patients should, however, be large enough to compensate for lower event rates or differences in baseline data.

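### The stated precision of the primary proportion (95% CI width 0.096) holds only if outcomes do not correlate within centre; it should be given as conditional, and the result reported with a centre-clustered interval

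*Protocol article*

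**What the plan says.** The sample size is justified only by precision. Under Sample size calculation, the article starts from "Assuming a calculated proportion of 0.76 for successes" and "a sample size of 300 for this subgroup", and concludes that "the width of the 95% CI, calculated using Wilson's method, will be 0.096 with the lower bound 0.709 and the upper bound 0.805". The abstract repeats these figures. The same paragraph plans recruitment at 45 centres with 4 patients per centre and year. No condition, ICC or design effect is attached to the width.

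Three other statements bear on the point:

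- Study design: "At the time of publication 45 neurologic and neurosurgical departments were registered as actively recruiting study centers", and "There will be no active allocation of the patients either to hemicraniectomy or any conservative treatment option". Treatment is thus left to routine care at each centre.
- Outcome measures: the primary outcome is mRS 0–4 against 5–6 at one year in patients who also meet the entry criteria of the randomised trials. As written, this subgroup is not limited to operated patients.
- Data analysis: 95% intervals are mentioned alongside group comparisons. No interval method is named for the primary proportion, and centre is not mentioned.

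**The concern.** A plain Wilson interval treats the 300 outcomes as independent draws with one common success probability. Here the patients are grouped by centre, and each centre decides whether and when to operate and how to manage the patient otherwise. If success rates differ between centres for these reasons, outcomes within a centre are correlated. A pooled one-group proportion contains no within-centre contrast in which a centre effect could cancel, so the between-centre variance enters its standard error in full. The Wilson formula leaves that variance out.

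Two things depend on this. The stated width is the only argument for 300 patients. The aim is also to see whether the trial result holds in daily routine, which is a statement about practice across centres. An interval that omits variation between centres would look more precise on that question than the data allow. The Discussion adds that the sample should suffice even for a more heterogeneous population than expected, but the calculation allows for no heterogeneity between centres.

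**Working it through.** **Inputs from the article:** p = 0.76, n = 300, two-sided 95% (z = 1.96), 45 centres. The mean number of subgroup patients per centre is m = 300/45 = 6.67.

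**Assumptions (not in the article):** ICC from 0.01 to 0.10; coefficient of variation (CV) of centre size 0 (equal centres) or 0.8 (unequal centres).

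**Step 1: reproduce the stated interval.** Wilson limits are [p + z²/(2n) ± z·√(p(1−p)/n + z²/(4n²))] / (1 + z²/n).

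- Midpoint: (0.76 + 0.00640)/1.01280 = 0.7567.
- Half-width: 1.96 × √(0.000608 + 0.0000107)/1.01280 = 0.0481.
- Result: 0.7086 to 0.8048, width 0.0963.

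This matches the article. A continuity-corrected Wilson interval (0.707 to 0.806) and a Wald interval (0.712 to 0.808) do not. The stated figure is therefore the independent-patient Wilson interval, correctly computed.

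**Step 2: allow for centre.** Design effect DE = 1 + [m(1 + CV²) − 1] × ICC, and effective sample size = 300/DE. The Wilson interval is recomputed at that size. Approximate coverage of the unadjusted interval is 2Φ(1.96/√DE) − 1.

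Example, ICC 0.05:

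- Equal centres: DE = 1 + 5.67 × 0.05 = 1.283; effective n = 234; coverage 2Φ(1.730) − 1 = 91.6%.
- CV 0.8: m(1 + 0.64) = 10.93; DE = 1 + 9.93 × 0.05 = 1.497; effective n = 200; coverage 2Φ(1.602) − 1 = 89.1%.

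| ICC (assumed) | CV | DE | Effective n | 95% CI | Width | Coverage of plain interval: formula / simulation |
|---|---|---|---|---|---|---|
| 0 | 0 | 1.00 | 300 | 0.709–0.805 | 0.096 | 95.0% / 95.1% |
| 0.01 | 0 | 1.06 | 284 | 0.707–0.806 | 0.099 | 94.3% / 94.5% |
| 0.02 | 0 | 1.11 | 269 | 0.706–0.807 | 0.102 | 93.7% / 93.9% |
| 0.05 | 0 | 1.28 | 234 | 0.701–0.810 | 0.109 | 91.6% / 91.8% |
| 0.10 | 0 | 1.57 | 191 | 0.695–0.815 | 0.120 | 88.3% / 88.1% |
| 0.01 | 0.8 | 1.10 | 273 | 0.706–0.807 | 0.101 | 93.8% / 93.7% |
| 0.02 | 0.8 | 1.20 | 250 | 0.703–0.809 | 0.105 | 92.7% / 92.3% |
| 0.05 | 0.8 | 1.50 | 200 | 0.696–0.814 | 0.118 | 89.1% / 88.5% |
| 0.10 | 0.8 | 1.99 | 151 | 0.686–0.821 | 0.135 | 83.5% / 82.8% |

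The simulated values come from beta-binomial outcomes in 45 centres, with 20,000 replicates per setting.

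**Step 3: what these ICCs mean.** The between-centre standard deviation of the success rate is √(ICC × 0.76 × 0.24). That is 0.043 at ICC 0.01 and 0.0955 at ICC 0.05.

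**Step 4: sample size for the stated width.** Keeping a width of about 0.096 needs 300 × DE patients: 317 (ICC 0.01) to 471 (ICC 0.10) with equal centres, and 330 to 599 with CV 0.8.

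**The case against.** The strongest reply is that nothing in the article is wrong as arithmetic and that the loss may be small. This largely stands. With equal centres and an ICC of 0.01 to 0.02, the width grows by only 0.003 to 0.006. Even at 0.05 with equal centres, coverage drops by about three points. A larger loss needs unequal centres or a higher ICC, and the article gives no figure for either. It also says that centres may keep joining ("The open design allows continuing initiation of cooperative study centers"), which would reduce the number of patients per centre.

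Several stronger readings are tempting but are not supported:

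- *That the interval does under-cover.* This needs an ICC above zero, and none is given. Treatment left to each centre makes one plausible but does not establish it.
- *That the Background proves a centre effect.* It reports that conservatively managed trial participants in intensive care "had a higher rate of survival (47% vs. 22%) and more often better functional outcome (mRS 0–4: 33% vs. 0%) than patients treated" at a lower level of care. Those figures compare two separate trials, not centres within one study. All registry centres are described as experienced in intensive care, with round-the-clock neurosurgical access. No ICC should be derived from these figures.
- *That plain Wilson is fixed as the analysis method.* It appears only as a planning figure. A statistical analysis plan, not shown here, may already provide a centre-robust interval.
- *That growth to 500 or 1000 patients would make matters much worse.* The Discussion mentions such growth as possible but does not tie it to the same 45 centres.
- *That the group comparisons are invalid* ("Two-sample *t* testing, the Mann–Whitney *U*-test, or *χ*2-testing will be used to analyze group differences as applicable"). Their p-values are called descriptive. Where both treatments occur in the same centre, ignoring centre can err in either direction, and no calculation here settles which.

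The article also sets no margin or interval-based rule for confirming the trial result, so no stated decision is overturned. What the reply does not answer is that the width is given without its condition, although it is the sole justification for the sample size.

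**Conclusion.** The concern holds in a limited, conditional form. The width of 0.096 is right if outcomes do not correlate within centre, and too optimistic if they do. With 6.7 patients per centre, the honest width is about 0.099 to 0.102 at an assumed ICC of 0.01 to 0.02 with equal centres, and about 0.109 to 0.118 at 0.05, depending on how unequal the centres are. Coverage of the plain interval is then about 94%, and about 92% to 89%, respectively. These figures rest on the assumed ICC and centre-size variation, on 45 centres, and on all 300 patients belonging to the primary subgroup. This is an inexpensive improvement to the stated precision and the reporting of the primary result. It is not an error that invalidates the design.

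**What to change.** 1. In Sample size calculation, and in the abstract that repeats it, make the precision conditional. For example: *width 0.096 if outcomes do not vary by centre; about 0.11–0.12 at an assumed ICC of 0.05*.
2. State that the primary proportion will be reported with a centre-clustered 95% CI. One workable form is a Wilson interval at the effective sample size n/DE, with DE from the centre-robust (Taylor linearisation) variance and a t quantile on centres minus one. SAS SURVEYFREQ with centre in the CLUSTER statement supports this, and SAS is already the planned software. In simulation at ICC 0.05, this interval covered 95.3% with equal centres and 94.6% with CV 0.6, against 91.8% and 89.4% for the plain interval.

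No change is asked for in the descriptive group tests or the log-rank analysis.

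The cost is wording, plus a slightly wider interval. Centre should be known for every patient, since each site sends its own case-report forms, so nothing further needs collecting. If there is no centre effect, the clustered interval averages about 0.102 against 0.096 (0.102/0.096 = 1.06, or 6% wider than needed) when the estimated design effect is not allowed to fall below 1.

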### Data analysis

All outcome measures will undergo descriptive data analysis, including mean, standard deviation, median, range, as well as absolute and relative frequencies depending on the scales of the variables. Additionally, descriptive *p*-values for group comparison and the corresponding 95% confidence interval will be indicated. Two-sample *t* testing, the Mann–Whitney *U*-test, or *χ*2-testing will be used to analyze group differences as applicable. Kaplan-Meier estimates and log-rank statistics will be used for assessing cumulative risk of death at 12 months. The comparability of different treatment groups will be depicted by comparing demographic and baseline data. Statistical analysis will be performed using the latest SAS software version (SAS Institute Inc., Cary, NC).

### Monitoring

Internal and external audits will be held in order to assure quality standards according to the Declaration of Helsinki, ICH-GCP guidelines, and governmental standards.

### Publication of the trial results

The trial results will be published independently of the results by the members of the Steering Committee and the participating centers (DESTINY-R study group). Authorship as well as publication of partial results will be regulated by the Steering Committee.

## Discussion

We advocate the use of a prospective register to further characterize patients with malignant MCA infarction and evaluate implementation, effectiveness and adverse events of current treatment concepts, including DHC. Although first trends in prevalence and outcome of DHC are promising and seem comparable to the results of the RCT
[23,24], the use of a large database allows the representation of a much broader population of patients treated for malignant MCA infarction. The anticipated sample size should allow confirming the results of the RCT and raising new hypotheses even if the population turns out to be more heterogeneous than expected. The planned inclusion of at least 300 patients in a reasonable time frame can only be achieved in a multicenter approach. The open design allows continuing initiation of cooperative study centers. The very conservative estimate of 4 patients/year per center would probably allow extending patient recruitment to 500 or even 1000 if certain questions would need a larger sample size to be investigated. However, due to the nature of a prospective registry, only hypotheses may be created, which then need further investigation in RCT.

To avoid the investigation of a very restricted group of patients, the inclusion criterion of infarct size was intentionally set comparatively wide. Thus any patient with a MCA infarction involving more than 50% of the territory can be included irrespective of treatment, although eligibility criteria for the RCT were infarction of more than 2/3 of the MCA territory. However, as the individual factors promoting infarct swelling are not well understood yet, not considering these patients may possibly exclude a subgroup of patients that would have the potential to benefit from a certain treatment option in the future. The limited number of eligibility criteria are easy to implement even in small hospitals with limited staff and will most likely result in a patient mix representative of clinical practice. Conservatively treated patients are followed simultaneously and constitute the control group, which may be compared to surgically treated patients in this parallel design. Due to treatment bias it may be possible that treatment groups show significantly different baseline data making a true comparison difficult. The expected number of patients should, however, be large enough to compensate for lower event rates or differences in baseline data.

The primary outcome measure is functional outcome after 1 year determined by the mRS score and dichotomized between 0–4 versus 5–6. This endpoint was chosen to ensure comparability with the results of the pooled analysis of the RCT. Secondary outcome measures were chosen following the aforementioned open questions that could not be answered in the RCT or have not been conclusively answered in clinical studies yet. They furthermore allow subgroup analyses, e.g. elderly patients, dominant-hemispheric infarction, and timing of treatment, some of which are currently under investigation in accompanying studies
[25].

The assessment of prognostic factors will lead to a better understanding of the risk of malignant infarct swelling and will aid clinical decision-making. We do not claim to assess causative associations in a cohort study. However, we expect to find predictive associations that will be of value in the immediate treatment process as well as in raising new hypotheses for subsequent treatment studies
[26].

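### The Discussion says patient numbers should compensate for baseline differences between operated and conservatively treated patients; sample size cannot remove treatment-selection bias, and the comparison tests named are unadjusted

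*Protocol article*

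**What the plan says.** Under Study design, the protocol article states: "There will be no active allocation of the patients either to hemicraniectomy or any conservative treatment option". The Discussion nevertheless sets up a comparison: "Conservatively treated patients are followed simultaneously and constitute the control group, which may be compared to surgically treated patients in this parallel design".

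For that comparison, Data analysis names the two-sample t test, the Mann–Whitney U test and the chi-square test, which "will be used to analyze group differences as applicable". For mortality, "Kaplan-Meier estimates and log-rank statistics will be used for assessing cumulative risk of death at 12 months". Baseline imbalance is handled by display: "The comparability of different treatment groups will be depicted by comparing demographic and baseline data". No regression, matching, weighting or stratification is named.

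The Discussion then acknowledges the problem, "Due to treatment bias it may be possible that treatment groups show significantly different baseline data making a true comparison difficult", and answers it in the next sentence: "The expected number of patients should, however, be large enough to compensate for lower event rates or differences in baseline data".

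Three statements limit what is claimed. Data analysis calls the p-values for group comparisons descriptive. The Discussion says that a registry can only create hypotheses for later randomised trials, and it disclaims causal associations.

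**The concern.** The compensating sentence joins two different problems. Low event rates are a problem of random error, and more patients help. Baseline differences that arise because clinicians choose who is operated on are a systematic error, and more patients leave it where it is. As the confidence interval narrows around the biased value, a false difference becomes more likely to look convincing.

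At stake are the comparisons of operated with conservatively treated patients on function, mortality and quality of life. The article calls the registry controlled, criticises earlier studies for lacking appropriate control groups, and promises information on the effectiveness of hemicraniectomy. A reader told that the numbers deal with baseline differences may give these comparisons weight that the design cannot support. The Discussion also contemplates extending recruitment to 500 or 1000 patients, where the misunderstanding does most harm.

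**Working it through.** **The plan's own figure.** Sample size calculation gives one number for precision: "Assuming a calculated proportion of 0.76 for successes in the subgroup of patients" and n = 300. The Wilson interval, with z = 1.96, is

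- centre = (p + z²/2n)/(1 + z²/n) = (0.76 + 0.0064)/1.0128 = 0.7567
- half-width = z·√(p(1−p)/n + z²/4n²)/(1 + z²/n) = 1.96 × √(0.000608 + 0.0000107)/1.0128 = 0.0481

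This gives 0.709 to 0.805, width 0.096, as stated. It describes one proportion in the subgroup meeting the RCT criteria. It says nothing about two treatment groups, so it cannot support the compensating sentence.

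**Does size compensate?** The article gives no treatment split, imbalance or group-specific outcome rates, so the inputs here are assumptions: no true treatment effect; equal groups; good outcome in 60% of patients without a poor-prognosis factor and in 30% with it. Three degrees of imbalance in that factor are tried.

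Crude success in a group with factor prevalence u is 0.60(1 − u) + 0.30u, so the spurious difference is 0.30 × (u_cons − u_op). N does not appear in it.

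- 45% operated vs 55% conservative: 46.5% vs 43.5%, difference 3 points
- 40% vs 60%: 48% vs 42%, difference 6 points
- 30% vs 60%: 51% vs 42%, difference 9 points

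The probability of rejection at two-sided 0.05 in the direction of the bias is Φ((d − 1.96·SE₀)/SE₁), with SE₀ pooled and SE₁ unpooled. For the third case at N = 300 (150 per group): SE₀ = √(2 × 0.465 × 0.535/150) = 0.0576; SE₁ = √((0.51 × 0.49 + 0.42 × 0.58)/150) = 0.0574; (0.09 − 0.1129)/0.0574 = −0.40; Φ = 0.345. Coverage is the chance that the crude 95% interval contains the true difference of zero.

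| Prevalence, operated vs conservative | Bias at every N | False rejection, N = 300 / 500 / 1000 | Coverage of zero, N = 300 / 500 / 1000 |
|---|---|---|---|
| 45% vs 55% | 3 points | 7.5% / 9.9% / 15.7% | 92% / 90% / 84% |
| 40% vs 60% | 6 points | 18% / 27% / 48% | 82% / 73% / 52% |
| 30% vs 60% | 9 points | 35% / 52% / 82% | 65% / 47% / 18% |

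The half-width of the interval falls from 11.2 to 8.7 to 6.2 points while the bias stays constant. With 70% of patients operated, the third case gives 30% / 45% / 74%. Exchanging the two prevalences reverses the sign and changes nothing else.

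**The case against.** The strongest reply is that this is one hedged Discussion sentence on which no sample size, endpoint or decision rule depends. The primary outcome is a single proportion with a confidence interval in the RCT-eligible subgroup, not a treatment comparison. The p-values are labelled descriptive, the results hypothesis-generating, and causality is disclaimed. All of this stands and limits the weight of the point. It does not make the sentence true: it follows directly on the admission of treatment bias and takes that caution back.

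A second reply is that this is a condensed article whose full protocol and analysis plan are not shown, and adjusted analyses are commonly specified there. That also stands. A reader might infer that no adjusted analysis is planned; the article does not say so, and the absence of a covariate model is not the finding. The finding is the claim about numbers, set beside the unadjusted methods that are named. A larger N can support adjustment for measured covariates, but the article credits the numbers themselves, and adjustment would still miss unrecorded reasons for operating.

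A third reply is that the illustration is invented. Its inputs are indeed assumed, which is why a range is shown. Only the constancy of the bias with N is general.

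**Conclusion.** The concern holds as an incorrect statement about what sample size can do, in a plan whose named comparison methods are unadjusted. It affects the secondary, comparative analyses. Under the assumed inputs the spurious difference is 3 to 9 points at any N, and false rejection rises from 7.5–35% at 300 patients to 16–82% at 1000.

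Three stronger readings are not supported:

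- A reader might infer that the primary result is biased in this way. It is one subgroup proportion and does not rest on the comparison.
- A reader might infer that the article presents the comparison as causal evidence. It uses the word effectiveness, but it also disclaims causality.
- A reader might infer that the bias must favour surgery. The documents do not say how treatment is chosen, only that treatment bias is possible. Inclusion from 50% of the MCA territory could bring milder cases into the conservative group, just as comorbidity or prior dependency could bring in worse ones.

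**What to change.** In the Discussion, delete the sentence's last clause, on baseline differences, or replace it with a statement that numbers improve precision but do not remove treatment-selection bias.

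In Data analysis, make the main comparison of hemicraniectomy with conservative treatment an adjusted one, by multivariable regression or propensity weighting with a check of overlap. If the full protocol or analysis plan already specifies this, refer to it. Use baseline variables recorded before treatment, such as age, medical history, pre-stroke mRS, NIHSS and infarct localization. Data collection lists the NIHSS with previous functional status, so confirm that a score for the index stroke is recorded. Do not adjust for onset-to-treatment time: time to surgery is listed for surgical procedures, with no counterpart for conservative patients. Report the unadjusted tests as descriptive only.

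State that residual confounding remains. This includes early death before possible surgery: such patients count as conservative, whereas every operated patient survived to the operation.

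The cost is wording and programming, and possibly wider intervals where the groups overlap poorly. The listed covariates need no new data if the NIHSS point is confirmed.
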